## Abstract

**Background:**

Adjustment disorder with anxiety (ADA) is the most frequent and best characterized stress-related psychiatric disorder. The rationale for prescription of benzodiazepine monotherapy is a public health issue. Cognitive behavioral stress management programs have been studied in many countries. Several reports have shown beyond reasonable doubt their efficiency at reducing perceived stress and anxiety symptoms and improving patient quality of life. Considering the number of people who could benefit from such programs but are unable to access them, self-help programs have been offered. First presented as books, these programs became enriched with computer-based and digital supports. Regrettably, programs for stress management based on cognitive behavioral therapy (CBT), both face-to-face and digital support, have been only minimally evaluated in France. To our knowledge, the Seren@ctif program is the first French language self-help program for stress management using digital supports.

**Objective:**

The aim of this study is to assess the effectiveness of a 5-week standardized stress management program for reducing anxiety conducted via eLearning (iCBT) or through face-to-face interviews (CBT) with patients suffering from ADA compared with a wait list control group (WLC). These patients seek treatment in a psychiatric unit for anxiety disorders at a university hospital. The primary outcome is change in the State Trait Anxiety Inventory scale trait subscale (STAI-T) between baseline and 2-month visit.

**Methods:**

This is a multicenter, prospective, open label, randomized controlled study in 3 parallel groups with balanced randomization (1:1:1): computer-based stress management with minimal contact (not fully automated) (group 1), stress management with face-to-face interviews (group 2), and a WLC group that receives usual health care from a general practitioner (group 3). Programs are based on standard CBT principles and include 5 modules in 5 weekly sessions that include the following topics: stress and stress reaction and assessment; deep respiration and relaxation techniques; cognitive restructuring, mindfulness, and acceptance; behavioral skills as problem solving; and time management, healthy behaviors, and emotion regulation. In the Internet-based group, patients have minimal contact with a medical professional before and after every session. In the first session, a flash memory drive is supplied containing videos, audio files, a self-help book portfolio in the form of an eGuide, and log books providing the exercises to be completed between 2 sessions. The patient is encouraged to practice a 20-minute daily exercise 5 or 6 times per week. In the face-to-face group, patients receive the same program from a therapist with 5 weekly sessions without digital support. Interviews and self-assessments were collected face-to-face with the investigator.

**Results:**

The feasibility of this program is being tested, and results show good accessibility in terms of acceptance, understanding, and treatment credibility. Results are expected in 2018.

**Conclusions:**

To our knowledge, this is the first French study to examine the effectiveness of a computer-based stress management program for patients with ADA. The Seren@ctif program may be useful within the framework of a psychoeducative approach. It could also be advised for people suffering from other diseases related to stress and for people with a clinical level of perceived stress.

**Trial Registration:**

Clinicaltrials.gov NCT02621775; https://clinicaltrials.gov/ct2/show/NCT02621775 (Archived by WebCite at http://www.webcitation.org/6tQrkPs1u)

## Introduction

### Background

Numerous studies have shown that exposure to a stressor increases the risk of psychiatric symptoms and disorders, especially anxiety. When anxiety symptoms are at a higher level than a normal reaction to a stressful event, we consider the possibility of a diagnosis of adjustment disorders, which are classified as stress-related disorders. They are responsible for significant direct and indirect costs from treatment, work stoppages, and loss of productivity [1].

### Adjustment Disorder With Anxiety

#### Definition

Adjustment disorder with anxiety (ADA) is the most frequent and best characterized stress-related psychiatric disorder [2]. According to the *Diagnostic and Statistical Manual of Mental Disorders, Fifth Edition* (DSM-5), a diagnosis of ADA is appropriate with the finding of anxiety occurring within 3 months of a psychosocial stressor or life event (eg, divorce, job loss, serious physical illness) [3] with symptoms generally abating by 6 months after the event. Considered a common disorder ranging from mild to moderate intensity, ADA is a true diagnostic entity. A general medical study showed that the level of anxiety is comparable to that of other anxiety disorders such as generalized anxiety disorder [4].

#### Current Recommendations for Adjustment Disorder With Anxiety

Patients are generally not treated with a tailored approach but with medication, mainly benzodiazepine monotherapy. Benzodiazepine misuse is a public health problem. Although stress management is considered the most appropriate psychological treatment for ADA, the evidence base for this approach is limited [5] **.** However, several studies compared cognitive behavioral therapy (CBT) with other treatments for generalized anxiety disorders and found greater improvements in stress and anxiety symptoms from CBT. In a study comparing CBT with relaxation, a posttreatment progression for State-Trait Anxiety Inventory scale (STAI-T trait subscale) scores from 53.04 to 46 and for Penn State Worry Questionnaire (PSWQ) scores from 61 to 51.13 were shown for the group that received CBT [6]. A study comparing psychodynamic psychotherapy with CBT found a greater improvement in the symptoms of stress and anxiety for the CBT intervention (a posttreatment progression of STAI-T trait subscale scores from 58.83 to 43.41 and of PSWQ scores from 63.48 to 49.86 in this group) [7]. In addition, eMental health options are considered uniquely suited for offering early intervention after patients experience stressful life events that can potentially trigger adjustment disorders [8].

#### Development of Preventive and Curative Measures for Adjustment Disorder With Anxiety

It seems legitimate, given the prevalence and the human, economic, and social costs of this pathology linked to stress, to develop preventive and curative measures for ADA. It is not always possible to intervene upstream to reduce the exposure to stress and prevent the occurrence of ADA (primary prevention). Secondary and tertiary prevention measures are therefore useful to limit their consequences.

### Stress and Anxiety Management

Stress management is a set of educational and psychotherapeutic measures that combines several cognitive behavioral techniques. The aim is to allow the patient to reach a satisfactory level of emotional and cognitive control and cope with stressors in order to reduce the negative consequences. The common practice is to offer group sessions or individual interviews in the form of a structured module limited in time [9].

### Cognitive Behavioral Therapy

CBT has been shown to be an effective treatment for reducing anxiety symptoms in various somatic pathologies such as cardiovascular disease [10,11], diabetes [12], chronic fatigue syndrome [13], and breast cancer [14] and in subjects with high levels of perceived stress or anxiety or burnout, particularly in the workplace [15]. A meta-analysis by Richardson and Rothstein [16] showed a moderate effect size (*d*=0.53) of stress management programs in the context of work, which is considered an average effect size according to the Cohen criteria [17]. For structured programs based on CBT, the effect is clearly greater (*d*=1) [9].

### Self-Help Therapy

Given that many patients do not have any access to stress and anxiety management programs, therapeutic education modules based on guides and self-help books have been offered and have shown positive results compared with classical CBT programs and control groups [18,19].

### Digital Stress Management

In recent years, the development of new technologies has enriched self-help programs by integrating new tools (CD-ROM, flash memory drive, or directly accessible on the Internet), allowing better interactivity and use other than contact with the therapist for patients [20].

These computer-assisted programs are intended to limit the amount of contact time with a mental health professional [21-23]. They have been evaluated in many countries in general, student, and corporate populations [24-36]. Unfortunately, computer-assisted programs have not been evaluated in France.

Recently, a meta-analysis evaluating the effect sizes of 26 computer- and Internet-based interventions was conducted on psychological stress and found significant results in terms of reduction of symptoms of stress (Cohen *d*=0.43, 95% CI 0.31-0.54), depression (Cohen *d*=0.34, 95% CI 0.21-0.48), and anxiety (Cohen *d*=0.32, 95% CI 0.17-0.47) compared to other types of interventions. These results provide evidence that Web- and computer-based stress management interventions can be effective and have the potential to reduce stress-related mental health problems on a large scale [37].

### Development of the Seren@ctif Program

It was in this context that Seren@ctif, a computer-based self-help management program, was developed at Lille University Hospital. It is the first French CBT program using digital support (iCBT). Seren@ctif is a neologism formed from 2 French words: seren for *serenité*, which means serenity, and actif, which means active and refers to self-help. The words are joined with an “at” sign to indicate the use of a digital format.

A pilot study was carried out between January and June 2014 to study the feasibility of this therapeutic program [38]. The results are satisfactory (average scores for satisfaction questionnaires were high, with scores ranging from 4 to 5 on a 5-point Likert scale). These results were the reason why it seemed appropriate to go further by evaluating this program in a controlled manner.

### Aims of the Study

The primary objective of this study is to assess the effectiveness of our stress management program conducted via e-learning (iCBT) or through face-to-face sessions compared with a wait list control (WLC) to reduce the anxiety level after 2 months in patients with a diagnosis of ADA.

The primary outcome is the change in the STAI-T score between the baseline and the 2-month visits.

The secondary objectives of this study are as follows:

Evaluate the maintenance of effectiveness of the 2 therapeutic stress management programs (iCBT and CBT) at 6 monthsCompare the change in stress, worry, anxiety, and depressive symptoms in the 2 therapeutic programs at 2 and 6 monthsMeasure the impact of the 2 therapeutic programs on the consumption of tobacco, alcohol, and drugsAssess overall satisfaction with the 2 therapeutic programs at 2 and 6 months and with the WLC at 6 months

The secondary outcome measures include the following:

Change in STAI-T scores at 6 monthsHospital Anxiety Depression Scale (HADS) anxiety subscale scores at 2 and 6 monthsWorry symptoms evaluated by the PSWQStress level evaluated by the Perceived Stress Scale (PSS) and the Visual Analog Scale–stress (VAS-stress) at 2 and 6 monthsDepressive symptoms evaluated by the Beck Depression Inventory (BDI) and the HADS depression subscale at 2 and 6 monthsOverall satisfaction evaluated by the VAS-satisfaction at 2 and 6 months for the 2 therapeutic groups and at 6 months for the WLC groupChange in consumption of tobacco, alcohol, and drugs evaluated at 2 and 6 months

### Hypotheses

We hypothesize that (1) both therapeutic programs will have a greater clinical impact on the reduction of anxiety symptoms, perceived stress, and depressive symptoms compared with a WLC in the short term (2 months), and this effect will be maintained in the long term (6 months); (2) the 2 therapeutic programs will have the same effectiveness in reducing these symptoms; (3) both therapies will be more cost effective than will WLC; (4) these 2 programs both reduce the consumption of tobacco, alcohol, and drugs compared with WLC; and (5) participants will be satisfied with the 2 therapeutic programs.

### Choice of Comparators

The comparison with the program implemented face-to-face is intended to highlight the value of eLearning, and the comparison with the control group, whose members receive general medical care, is intended for comparison with the current recommendations for therapeutic studies.

### Prospect of the Project

The future goal of this project is to enrich the program with new information and communication technologies, such as the Internet (eCBT) [39-41] and mobile (mCBT) options [42-45], and propose the program to a large population for prevention of stress-related disorders.

## Methods

### Setting and Procedure

#### Type of Study

It is a multicenter, comparative, prospective, unblinded, randomized, controlled study in 3 parallel groups. As it is not possible to mask the different treatment groups, patients were not blinded from their intervention group.

#### Ethics

The project was approved by the local ethics committee, *Comité de Protection des Personnes Nord Ouest IV* (approval number CPP 15/12), as is required for medical intervention research in France. Data processing will be carried out in accordance with the requirements of the *Commission Nationale de l’Informatique et des Libertés* reference methodology, MR 06001 (Multimedia Appendix 1).

#### Recruitment

The study is being conducted at 3 university hospitals (Lille, Amiens, Caen) in the northwest area of France as part of the university communities (*InterRégional*). Patients are referred by their general practitioner to a psychiatric consultation service for psychological treatment of anxiety symptoms in a context of recent stress. To improve recruitment, general practitioners in the 3 areas were informed of the study by a local investigator during continuing medical education, during scientific meetings, and through all types of collaborative contacts between primary care and psychiatry services. We also directly informed the general practitioners who were involved in previous research on ADA and CBT and invited them to refer patients.

#### Agreement of the Subjects

During a medical interview, participants will receive oral and written information detailing the progress of the trial and be allowed a period of reflection. Informed consent will be collected from each subject before they enter the study (Multimedia Appendix 2).

#### Criteria for Discontinuing Participation in the Study

Participants are told they are free to leave the study at any time. Participants will be released from the study by the investigator in cases of adverse events such as diagnosis of an illness requiring hospitalization or surgery, beginning a new medication, or changing medication doses. The current research does not involve any risk, with the exception of the possible negative psychological impact of completing the psychological questionnaires.

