#### Computer-Based Stress Management Program

The program includes 5 weekly sessions lasting 1 hour that patients follow from a program accessible on a computer in our unit.

Participants have minimal contact with a clinician to encourage adherence and engagement with the program. This minimal contact of 5 minutes is performed before and after every session by a trained nurse, who investigates the adverse events and drug dose changes since the last session, answers any questions, discusses the progress of the session, and possibly guides participants in the navigation of the computer program.

To avoid connection problems, a flash memory drive is supplied to the participant at the first session that contains videos, audio files, self-help books, a portfolio in the form of an eGuide, and a log book with the program of exercises to be completed between 2 successive sessions of the program. The patient is encouraged to practice 1 or several daily exercises for 20 minutes each, 5 or 6 days per week (Multimedia Appendix 3).

Selection criteria.Inclusion criteria:Ambulatory patient (as inpatients are frequently a mixed anxiety depressive type of adjustment disorder)Male or female aged 18 to 60 years (we use a cutoff age of 60 years for inclusion to limit chronic somatic comorbidities)Diagnosis of adjustment disorder with anxiety (ADA) according to the *Diagnostic and Statistical Manual of Mental Disorders, Fifth Edition* criteriaCurrently not supported by structured psychotherapeutic treatment for ADA or any other problemTaking no new psychotropic drug therapy or stabilized for at least 3 months (in the latter case, the patient will be informed of the need to keep the same dosages for the duration of the study)Minimum score on the Hospital Anxiety and Depression scale (HADS) anxiety subscale greater than or equal to 10 and a maximum score on the HADS depression subscale of less than 10Access to a computerExclusion criteria:Inability to read or use a computer with support (the platform is easy-to-use and a nurse is available to guide the patient in the navigation of the computer program)Pregnancy (as recommended by the French ethics committee; urine pregnancy test performed on female patients)Not capable of consenting, not having legal protection, or being deprived of libertyDiagnosis of another psychiatric disorder (according to the Mini International Neuropsychiatric Interview)

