#### Stress Management by Face-to-Face Interviews

The program includes 5 weekly sessions lasting 45 minutes or 1 hour with trained clinical psychologists (graduate of a master’s program in cognitive and emotional therapy with a minimum of 1 year of practice in CBT and cognitive behavioral stress management). Information, exercises, and homework assignments are delivered by the therapist without self-help support. At the beginning of each session, the therapist asks the participant about adverse events and changes in drug doses since the last session.

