#### Wait List Control

Control group patients received usual care consisting of contact with their general practitioner and nonspecific psychoeducation about stress and anxiety. Medication is prescribed as a stable dose during the period prior to assessment at 2 months.

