### Statistical Analysis

#### Overview

Statistical analysis will be conducted in a blinded fashion with a blinded code for the intervention. All statistical analyses will be carried out independently in the Department of Biostatistics of the University Hospital of Lille. SAS 9.3 (SAS Institute Inc) software or later will be used. *P* values will be reported as the actual values, unless *P*<.001. No interim analyses are planned. A detailed statistical analysis plan (SAP) will be drafted and validated before the database is frozen. Patient characteristics at baseline will be described for each of the 3 arms; the quantitative variables will be described either by the mean and standard deviation in case of a Gaussian distribution or by the median and interquartile range if not. The normality of the distributions will be verified graphically by histograms and by the Shapiro-Wilk test. The qualitative variables will be described by the numbers and percentages of each category. All analyses for the primary and secondary objectives will be performed on all randomized patients in their original group of randomization according to intention-to-treat (ITT) principles. No subgroup analysis will be performed.

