#### Main Objective

Comparison of the primary endpoint (2-month change in STAI scale) between each experimental group and the control group will be performed separately using an analysis of covariance with an adjustment for the STAI baseline value and the center. Since 2 comparisons will be made for the primary analysis, each of them will be performed at the 2.5% significance level (Bonferroni correction). The absolute mean differences and effect sizes (standardized mean difference) will be reported with the 95% confidence interval. In case of deviation from normality of model residuals, nonparametric analysis will be used; absolute changes between baseline and 2-month visits will be calculated and compared between the experimental arm and control arm using nonparametric analysis of covariance adjusted for baseline values [63,64]. The primary analysis will be conducted according to the ITT principle. Missing values will be handled by multiple imputation procedures. Missing data will be imputed under the missing at random assumption using a regression switching approach (chained equation with m=20 imputations) with predictive mean matching method for continuous variables and logistic regression (binary, ordinal, or polynomial) for qualitative variables [65]. The imputation procedure will be performed using the main baseline characteristics, outcome, and variable group of randomization, and multiple imputed data sets will be combined using Rubin’s rules [66,67]. Sensitivity analyses will first be conducted using all available STAI measurements (complete cases analysis) and second in patients without major deviation from protocol (per protocol analysis); major deviations will be specified in the SAP.

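### Medication changes and intercurrent illness release a patient from the study rather than only from the program, so outcomes that the intention-to-treat analysis needs are lost and must be imputed

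*Protocol article*

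**What the plan says.** Under Criteria for Discontinuing Participation in the Study, the article states: "Participants will be released from the study by the investigator in cases of adverse events such as" and then lists "diagnosis of an illness requiring hospitalization or surgery, beginning a new medication, or changing medication doses". The release is from the study, not from the program. The article makes no distinction between stopping treatment and stopping follow-up, and it gives the rule no end date.

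Other sections bear on how often the rule would apply:

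- **Usual treatment.** The background on current recommendations says: "Patients are generally not treated with a tailored approach but with medication, mainly benzodiazepine monotherapy".
- **Program arms.** Each computer session includes contact with a nurse "who investigates the adverse events and drug dose changes since the last session". In the face-to-face arm, "the therapist asks the participant about adverse events and changes in drug doses since the last session".
- **Wait list.** "Medication is prescribed as a stable dose during the period prior to assessment at 2 months". No contact by the study team is described between baseline and the 2-month visit.
- **All arms.** The selection criteria tell patients already on stabilized psychotropic drugs to hold their doses throughout the study.
- **Visits.** Assessments says all three groups are seen at baseline, 2 months and 6 months.

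On analysis, the Overview says all primary and secondary analyses "will be performed on all randomized patients in their original group of randomization according to intention-to-treat (ITT) principles". Main Objective adds: "Missing data will be imputed under the missing at random assumption".

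**The concern.** An intention-to-treat analysis needs the outcome of every randomized patient, including those whose treatment changed. A rule that ends study participation at a medication change works against that aim. It removes a self-report score that could still have been collected at a visit already in the schedule.

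The loss may not be random. Persisting anxiety is a plausible reason to start or raise an anxiolytic, and anxiety is the primary outcome. Imputation under missing at random then fills the gap from patients who look alike at baseline but did not need the change.

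Detection may also differ by arm. Program patients are asked about doses every week. For the wait list, the first follow-up contact described is the 2-month visit itself, where the primary outcome is collected. At stake are some precision and a bias of unknown sign in each comparison of a program with the wait list.

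**Working it through.** **1. The plan's own figure.** Inputs from Sample Size: difference 11.5 (the mean of 7 and 16), SD of change 14.6, correlation 0.5, type I error 2.5% per comparison (taken as two-sided), power 80%, 20% missing data.

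- SD of change: 14.6 × √(2 × (1 − 0.5)) = 14.6, as stated.
- Normal approximation: n = 2 × (2.2414 + 0.8416)² × 14.6² / 11.5² = 30.6, so 31 per group. The noncentral t gives 32 (power 80.1%), which matches the plan.
- Inflation: 32 / 0.8 = 40 per group, 120 in total. This also matches.

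With all 40 per group measured, power is 89.0%. The 20% allowance therefore covers lost precision. It does not cover bias from outcome-related loss.

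**2. Yardstick.** Standard error of the baseline-adjusted difference with 40 per arm: 14.6 × √0.75 × √(2/40) = 2.83. With 32 per arm it is 3.16.

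**3. Possible bias.** The article gives no release rates, so every rate below is an assumption. Large-sample simulation: baseline mean 52.1, SD 14.6 at both times, correlation 0.5, true benefit 11.5. The log-odds of release equal a + b × (2-month score − 52.1)/14.6. The estimate is the baseline-adjusted difference among retained patients. In large samples this is close to imputation from baseline STAI-T and group when released patients have no later data.

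| Assumption | Released, wait list / program | Estimated benefit | Shift |
|---|---|---|---|
| Unrelated to outcome (b = 0) | 17% / 7% | 11.49 | about 0 |
| Same rule in both arms (b = 1) | 7% / 3% | 11.15 | −0.35 |
| Same rule in both arms | 13% / 7% | 10.91 | −0.59 |
| Same rule in both arms | 21% / 12% | 10.64 | −0.86 |
| Wait-list changes found only after the 2-month score | 0 / 3% | 11.85 | +0.35 |
| Wait-list changes found only after the 2-month score | 0 / 7% | 12.22 | +0.72 |
| Wait-list changes found only after the 2-month score | 0 / 12% | 12.65 | +1.15 |

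If half of the wait-list changes are found in time, the three estimates are 11.52, 11.61 and 11.76 (shifts of +0.02 to +0.26). If further baseline variables in the imputation explain 40% of the residual variance, the same-rule shifts shrink to −0.21 (7%/3%) and −0.54 (21%/12%).

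A second model ties release to the part of the 2-month score that baseline and arm do not explain (log-odds rising by 1 per SD) and fixes the release rates directly. It gives 10.9 at 10%/5%, 10.4 at 20%/10%, 9.9 at 20%/5% and 9.5 at 30%/10%. These are shifts of about −0.6 to −2.0.

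**4. Low release.** The article reports one subject lost, with 50 of 120 enrolled. At release near that level (2.6% / 1.2%, first model) the estimate is 11.34 under the same rule, 11.50 if half of wait-list changes are found in time, and 11.66 if none are. The largest shift is 0.16 points.

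Across all scenarios, the largest shift (about 2.0) stays below the standard error of 2.83.

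**The case against.** Several points count against a stronger claim.

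- **Stable dosing.** A reader might infer that dose changes are unrestricted after 2 months, because the wait-list statement stops there. The selection criteria do not support that: patients on stabilized drugs in every arm are told to hold their doses to the end. The triggers may be infrequent. What remains is that a request does not prevent changes, and it does not address new starts.
- **Wait-list monitoring.** A reader might infer that medication in the wait list goes unrecorded. Assessments has medications recorded at baseline and further items added at 2 and 6 months for all groups, so medications are plausibly recorded again at those visits. The gap is only between baseline and 2 months.
- **Adverse-event wording.** The triggers are given as examples of adverse events, so release may not follow every change. They are still named grounds for release.
- **A condensed article.** The full protocol may collect questionnaires at release. The planned per-protocol analysis also suggests that some patients who deviate have outcome data. But the article states the release rule itself, and an analysis plan cannot recover questionnaires that were not collected.
- **Holding medication constant is deliberate.** An analysis aimed at the program effect without added drugs would set post-change scores aside anyway. That is a legitimate aim, but the stated one is intention to treat for all randomized patients, and the per-protocol analysis can serve the other.
- **Small impact.** This stands. All release rates are assumed, and the single reported loss points to a low rate, although follow-up was incomplete and its reason is not given.

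**Conclusion.** The point holds as a design weakness with a cheap remedy. Followed as written, the release rule discards outcomes that the intention-to-treat analysis needs and leaves them to imputation under an assumption that the triggers may violate. The loss is avoidable.

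A reader might infer that the primary comparison is biased in a known direction or by a material amount. The documents do not support that. The shift is zero if release is unrelated to outcome. It runs against the program if one outcome-dependent rule applies equally, and in its favor if wait-list changes surface too late. Under the assumed rates it ranges from about −2.0 to +1.15 points on a benefit of 11.5, and at release near the reported loss it is at most 0.16.

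These figures rest on the plan's SD and correlation, a logistic release model and assumed release rates. Changes after the 2-month visit would affect only the 6-month secondary outcomes.

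**What to change.** Amend the discontinuation criteria so that a medication start, a dose change or an intercurrent illness may stop or flag the intervention but does not end follow-up. Collect the 2- and 6-month questionnaires from every randomized patient who has not withdrawn consent, and use the observed scores in the intention-to-treat analysis. Where this is not already done, record the date and type of each medication change in all three arms. The planned per-protocol analysis can exclude patients whose medication changed. A sensitivity analysis that departs from missing at random is optional and can be left to the analysis plan.

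**Cost.** The amendment is short but may need ethics review, and patients already released will have followed the old rule. The visits are already scheduled. Even if the whole 20% allowance were due to release, the extra work is at most 0.20 × 120 = 24 patients × 2 visits = 48 visits, and probably far fewer.

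**Downside.** The estimate then includes the effect of any added medication. With an assumed 7-point drug effect, the benefit falls by (0.069 − 0.034) × 7 = 0.25 points at 7%/3%, or (0.207 − 0.115) × 7 = 0.64 points at 21%/12%. That is part of the effect of assignment, not a bias.
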